**VII. Efficacy Evaluation Criteria**

1. **Efficacy Evaluation:** Measure the impact of blood flow rate on filter lifespan in anticoagulant-free CRRT, recording each patient's blood flow rate, filter usage time, and any potential filter failures or blockages.
2. **Safety Evaluation:** Monitor adverse events related to blood flow rate adjustments, such as thrombus formation, bleeding, or filter failure, continuously monitoring and recording the occurrence and severity of adverse events in each patient. Use statistical methods to analyze the incidence of adverse events and compare them with different blood flow levels to assess their correlation.

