- **Stepwise Reduction of Blood Flow Rate:** The blood flow rate will be reduced in increments of 50 mL/min, observing the patient's response and filter performance until a stable state is achieved.
- **Assessment and Recording:** After each adjustment, detailed records will be kept of the blood flow rate before and after adjustment, filter performance, patient's clinical manifestations, and reasons. Clinical judgment will be made based on the patient's actual condition to decide whether further adjustment is needed and to ensure patient safety and treatment efficacy. During data analysis, intention-to-treat analysis and per-protocol analysis will be used separately.
- **Record Filter Lifespan and Adverse Events:** Record the lifespan of the filters in the three groups, as well as the occurrence of clotting events and other negative events related to CRRT such as hypotension.

1. **Research Steps**

[Diagram]

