**IV. Case Selection**

1. **Inclusion Criteria**
   1. Patients undergoing CRRT;
   2. Age 18 years or older;
   3. No anticoagulant used during CRRT;
   4. Informed consent provided by the patient or their legal guardian/agent.
2. **Exclusion Criteria**
   1. Patients with severe coagulation disorders or undergoing anticoagulant therapy;
   2. Patients receiving intermittent renal replacement therapy (IRRT) or other non-CRRT treatments;
   3. Pregnant women.
3. **Criteria for Study Termination**
   1. **Safety Issues:** Serious adverse events: If during the study, the incidence of serious adverse events related to treatment such as hypotension, malignant arrhythmias, or death is significantly higher in one group compared to the other two groups, or exceeds the predefined safety threshold, consideration should be given to terminating that group's study. The safety threshold is set based on data from similar previous studies and the opinions of clinical experts to ensure patient safety. For example, if the incidence of bleeding events exceeds 10% and is 5% or more higher than the other groups; the incidence of thrombotic events exceeds 5% and is 3% or more higher than the other two groups; the incidence of infectious events exceeds 15% and is 5% or more higher than the other groups; the incidence of cardiovascular events exceeds 8% and is 4% or more higher than the other two groups [2,3].
   2. **Inadequate Effectiveness:** Interim analysis: Interim analysis will be conducted after 50% of the patients have been enrolled, performed by an independent statistician who is blinded to treatment allocation.
   3. **Interim Analysis Objectives:** To assess filter lifespan in different blood flow rate groups, compare filter blockage rates among groups, and evaluate the incidence of adverse events.
   4. **Interim Analysis Indicators:** Primary outcome measure: Filter lifespan (hours); Secondary outcome measures: Filter clotting rate, incidence of adverse events (bleeding, thrombus formation, etc.).
   5. **Interim Analysis Method:** Kaplan-Meier survival analysis will be used to assess filter lifespan, and the Log-rank test will be used to compare differences in filter lifespan among different groups. The chi-square test will be used to compare differences in filter blockage rates and adverse event incidence among groups.

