   6. If the interim analysis results show that the filter lifespan in any group is significantly lower than the other groups (P < 0.05), and the incidence of adverse events is significantly increased, enrollment of patients in that group will be terminated. If there is no significant difference in filter lifespan among all groups (P > 0.05), and no significant difference in adverse event incidence, the study will continue until all patients have been enrolled.
   7. The statistician will report to the independent Data and Safety Monitoring Board (DSMB), which will review and assess the interim analysis data and provide recommendations to the researchers on whether to continue, modify, or terminate the study [4][5].
   8. **Achievement of Statistical Significance:** If the interim analysis shows a significant difference in filter lifespan among different blood flow rate groups (P < 0.05), and this difference is sufficient to prove the primary research hypothesis, the study may be terminated early.
   9. **Participant Request to Withdraw:** If a participant requests to withdraw from the study.

**Termination Procedure:** Upon receiving the DSMB's recommendation, the study leader should immediately suspend enrollment of new patients and notify all research centers; inform the Institutional Review Board (IRB) and relevant regulatory authorities, providing the reasons for termination and the interim analysis results; provide appropriate follow-up treatment and follow-up for patients already enrolled.

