**VIII. Observation, Recording, and Management of Adverse Events**

In this study, adverse events refer to events during CRRT that cause CRRT to be urgently stopped or pose a life-threatening risk to the patient, with significant improvement after CRRT is stopped. Therefore, the observation of CRRT adverse events ends when the patient completely finishes multiple courses of CRRT.

Anticipated adverse events include hypotension, electrolyte imbalance, bleeding, or infection. The relationship between adverse events and study interventions is typically judged based on: 1) Temporal association: The event occurs within a specific time after CRRT initiation, or other causes of adverse events are excluded; 2) Known side effects of drugs or devices; 3) Whether the event disappears or alleviates after CRRT is stopped.

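### Filter failure is listed both as an efficacy measure and as an adverse event, and the protocol never says whether thrombus means the patient or the circuit

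*Protocol*

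**What the plan says.** All references are to the protocol.

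- **Section VII, item 1 (efficacy)** asks for "recording each patient's blood flow rate, filter usage time, and any potential filter failures or blockages".
- **Section VII, item 2 (safety)** says "Monitor adverse events related to blood flow rate adjustments, such as thrombus formation, bleeding, or filter failure", and then "Use statistical methods to analyze the incidence of adverse events and compare them with different blood flow levels".
- **Section III, Research Methods**, in the bullet on recording filter lifespan and adverse events, asks for "the occurrence of clotting events and other negative events related to CRRT such as hypotension". Clotting is thus one kind of negative event.
- **Section VI, item 2** makes visible clotting of the filter, catheter or venous chamber the first criterion for replacing a filter. It is one of the events that end filter life, the primary outcome.
- **Section IV.3, item 4 (interim indicators)** lists as secondary measures "Filter clotting rate, incidence of adverse events (bleeding, thrombus formation, etc". Filter clotting stands beside adverse events, not inside them, and item 5 tests filter blockage and adverse event incidence as two measures.
- **Section IV.3, item 6** closes an arm if "filter lifespan in any group is significantly lower than the other groups (P < 0.05), and the incidence of adverse events is significantly increased".
- **Section IV.3, item 1** gives as an example of a safety threshold that "the incidence of thrombotic events exceeds 5% and is 3% or more higher than the other two groups".
- **Section VIII** says that "adverse events refer to events during CRRT that cause CRRT to be urgently stopped" or that threaten life, adds that there should be marked improvement once CRRT stops, and anticipates hypotension, electrolyte imbalance, bleeding and infection.

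Nowhere does the protocol say whether thrombus formation or thrombotic events refers to the patient or to the circuit. Section I uses thrombus formation, next to filter clotting, for something that shorter dwell time in the filter should reduce.

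**The concern.** Filter lifespan is the primary outcome, and clotting is one of the things that end it. If filter failure is also counted in the adverse event incidence, a flow rate that only shortens filter life will also appear less safe, even if no patient is harmed more often. The safety comparison in Sections VII and XI would then partly report the primary outcome a second time, and differences in bleeding, hypotension or patient thrombosis would be harder to see within the pooled count.

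The arm-closing rule in Section IV.3 item 6 needs two conditions: shorter filter life and more adverse events. The second condition is useful only if it is separate evidence about patients. If filter failure counts toward it, shorter filter life helps to produce the increase in adverse events.

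**Working it through.** **Step 1. The sections side by side**

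| Section | Filter failure or clotting counted as an adverse event? |
|---|---|
| III, Research Methods | Clotting grouped with other negative events |
| IV.3 items 4 and 5 | No: a separate indicator and a separate test |
| IV.3 item 6 | Not stated; uses adverse event incidence |
| VII item 1 | Efficacy |
| VII item 2 | Yes: filter failure named |
| VIII | Not named; anticipated events are patient harms |

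Section VII is explicit about the double listing. Sections IV.3 and VIII point the other way, and no sentence says which governs.

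**Step 2. How far it reaches**

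- The final safety comparison is affected directly, because Section VII item 2 names filter failure and then calls for adverse event incidence to be compared across flow levels.
- Item 6 of Section IV.3 is affected if the Section VII list is the one used for it.
- The thrombotic limit in item 1 is affected only if thrombotic events is read to include circuit clotting.

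**Step 3. Illustration of size**

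The protocol states no event rate, so there is no figure of its own to reproduce. Inputs:

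- Patients per arm at the interim: 486 × 50% / 3 = 81. This takes the 486 cases in the abstract as patients; Section III counts 486 filters.
- Patient-harm rate h: assumed equal in all arms, 10% or 20%.
- Filter failure rate f: assumed, differing by arm.
- One record per patient, with harm and failure independent.
- Three-group chi-square test (Section IV.3 item 5) at 0.05, 2 degrees of freedom.

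The rate with any counted event is q = 1 − (1 − f)(1 − h). For f = 60/50/40%:

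- h = 10%: q = 1 − 0.4×0.9, 1 − 0.5×0.9, 1 − 0.6×0.9 = 0.64, 0.55, 0.46
- h = 20%: q = 0.68, 0.60, 0.52

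The noncentrality is λ = n Σ(qᵢ − q̄)² / [q̄(1 − q̄)]:

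- h = 10%: 81 × (2 × 0.09²) / (0.55 × 0.45) = 1.3122 / 0.2475 = 5.30
- h = 20%: 81 × (2 × 0.08²) / (0.60 × 0.40) = 1.0368 / 0.24 = 4.32

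Share of simulated trials (400,000 per row) with a significant adverse event test:

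| Filter failure by arm | λ (h = 10%, 20%) | Failure counted | Patient harm only |
|---|---|---|---|
| 60/50/40% | 5.30, 4.32 | 53%, 44% | about 5% |
| 30/20/10% | 6.51, 4.50 | 63%, 46% | about 5% |
| 70/50/40% | 12.57, 10.34 | 91%, 85% | about 5% |
| 55/50/45% | 1.33, 1.08 | 16%, 14% | about 5% |
| 50/50/50% | 0, 0 | about 5% | about 5% |

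Patient harm is equal across arms in every row. The excess over 5% comes only from the difference in filter failure. At full enrolment (162 per arm) λ doubles for the same rates, so the effect on the final comparison would be larger.

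**The case against.** **The interim section already separates the concepts.** Items 4 and 5 of Section IV.3 treat filter clotting or blockage and adverse events as different measures, and item 6 follows in the same section. The natural reading of item 6 uses that separation. This stands: the effect on item 6 is conditional.

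**Section VIII points to patients.** A reader might infer that a clotted circuit meets its definition because CRRT has to stop urgently. But the definition adds improvement after CRRT stops, which describes a patient's condition and not a clotted filter, and the anticipated events are all patient harms. The stronger inference is not supported. This also means that Section VIII conflicts with Section VII item 2.

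**The thrombotic limit.** A reader might infer that circuit clotting would routinely breach it and close an arm. The documents do not support that. The limit is introduced as an example within a rule about serious events such as hypotension, malignant arrhythmia or death; a breach leads only to consideration of termination, and an independent board reviews the interim data. Simulated breach rates would not measure double counting either. With assumed failure of 60/50/40% and patient thrombosis of 2%, some arm breaches in about 85% of trials, but with identical failure of 50% in every arm some arm still does in about 58%. Much of that is chance variation around a 3-point margin at high event rates.

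**Filter endings by 24 hours.** Gamma distributions fitted to the means and SDs in the sample size section give 52% of filters ended by 24 h at 200 mL/min and 29% at 250 mL/min. These are endings for any reason. Section VI also ends filters at 72 hours, for outside examinations or other treatment, and when goals are met or CRRT stops. They are not clotting rates and cannot be set against an adverse event limit.

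**Recording device failure under safety is not wrong in itself**, and item 2 names failure where item 1 names failures or blockages. This is fair, but neither word is defined, Section III groups clotting with negative events, and the incidence is to be compared with nothing said about keeping the two kinds of event apart.

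**Conclusion.** The point holds as an inconsistency in what counts as an adverse event. Section VII lists filter failure under both efficacy and safety, Section III leans the same way, and Sections IV.3 and VIII keep filter clotting apart or anticipate only patient harms. Followed as written, Section VII makes the final safety comparison partly repeat filter lifespan; this does not depend on any stopping rule being triggered.

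The consequence for item 6 of Section IV.3 depends on which list is applied there. The consequence for the thrombotic limit depends on reading an undefined term to include the circuit. Neither should be stated as fact.

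On size, with 81 per arm, equal patient harm of 10–20% and failure of 60/50/40%, the adverse event test is significant in about 44–53% of trials instead of about 5%. Across the other unequal failure rates tried, the range is about 14% to 91%. These are illustrations under assumed rates and independence, and they concern the adverse event test alone, not the joint probability that item 6 closes an arm.

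**What to change.** - In Section VII item 2, delete filter failure from the adverse events.
- Reconcile Sections III, IV.3, VII and VIII so that clotting of the filter, circuit or venous chamber is reported only as the filter clotting rate. It should not count in adverse event incidence or in the second condition of Section IV.3 item 6.
- State that thrombus formation and thrombotic events, when used as adverse events, mean thrombosis in the patient.
- Say where catheter clotting belongs, since Section VI item 2 lists it with filter and venous chamber clotting.
- Keep recording any clinical consequence of circuit clotting as an adverse event, so that no patient safety information is lost.

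The cost is a few sentences and one extra field on the data form. Headline adverse event rates will be lower, which the report should explain. The definition should be settled before any comparison by arm is seen, because afterwards the choice could alter which flow rate appears less safe.

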**VIII. Observation, Recording, and Management of Adverse Events**

In this study, adverse events refer to events during CRRT that cause CRRT to be urgently stopped or pose a life-threatening risk to the patient, with significant improvement after CRRT is stopped. Therefore, the observation of CRRT adverse events ends when the patient completely finishes multiple courses of CRRT.

Anticipated adverse events include hypotension, electrolyte imbalance, bleeding, or infection. The relationship between adverse events and study interventions is typically judged based on: 1) Temporal association: The event occurs within a specific time after CRRT initiation, or other causes of adverse events are excluded; 2) Known side effects of drugs or devices; 3) Whether the event disappears or alleviates after CRRT is stopped.

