**VI. Detection Items and Time Points**

1. **Baseline Data:** At the time of patient admission, detailed records will be kept of demographic characteristics, laboratory indicators, examination results, primary disease, comorbidities, concomitant medications, blood pressure, etc.
2. **Filter Lifespan:** Each time a filter is replaced, the usage time of each filter will be recorded. Filters will be replaced based on the following criteria: obvious clotting in the filter, catheter, or venous chamber; filter usage time exceeding 72 hours (even if there are no other issues); patient needs to stop the machine for an outside examination or other treatments; treatment goals are achieved or CRRT is terminated.
3. **CRRT-Related Parameters:** After the CRRT prescription is established, detailed records will be kept of the CRRT prescription, including ultrafiltration rate, access, mode, etc. If the blood flow rate is reduced due to poor circuit performance or the anticoagulation method is adjusted due to coagulation function, the time, adjustment amount, and changes before and after adjustment will be recorded in detail.
4. **Filter Performance and Efficacy:** After CRRT is completed, the filter clearance performance will be recorded, including creatinine clearance, urea nitrogen clearance, cystatin C, and ultrafiltration rate.
5. **Patient Physiological Parameter Changes:** During CRRT, arterial blood pressure will be monitored every 2 hours, and the occurrence of hypotension and other hemodynamic instability events will be recorded.
6. **Adverse Events:** During CRRT, any adverse events that occur will be observed and recorded, including thrombus formation, bleeding complications, etc.
7. **Clinical Outcomes:** After CRRT is stopped, the patient's renal function recovery will be monitored, such as changes in creatinine and glomerular filtration rate. After discharge, the patient's survival status and hospital stay duration will be recorded.

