**Recording, Management, and Reporting of Adverse Events:**

1. **Recording:** All adverse events, regardless of severity or expectation, should be meticulously documented in the study records. The documentation should include a description of the event, its severity, start and end dates, management measures, outcomes, and an assessment of the association with the study treatment.
2. **Management:** For any serious or unexpected adverse events, appropriate therapeutic measures should be immediately taken. For instance, in the case of hypotension, measures such as reducing ultrafiltration and administering fluids to raise blood pressure should be implemented. In the event of an allergic reaction, timely administration of dexamethasone and antihistamines may be necessary, which could also include discontinuing the study intervention.
3. **Reporting:** All serious adverse events will be reported to the supervising physician regulatory authorities and the ethics committee within the stipulated timeframe. Additionally, in accordance with local regulations and protocol requirements, these events will be reported to the relevant regulatory bodies.

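### Section VIII's adverse-event definition contradicts the rest of the protocol, so it is not fixed which events enter the safety comparison and the stopping rule

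*Protocol*

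**What the plan says.** The only definition of an adverse event is in Section VIII: "adverse events refer to events during CRRT that cause CRRT to be urgently stopped or pose a life-threatening risk to the patient". The sentence adds an outcome condition: the event must "pose a life-threatening risk to the patient, with significant improvement after CRRT is stopped" (the clause may govern both limbs or only the second). The next sentence draws the observation window from this: "Therefore, the observation of CRRT adverse events ends when the patient completely finishes multiple courses of CRRT". The same section then uses improvement again as one of three criteria for relatedness: "Whether the event disappears or alleviates after CRRT is stopped".

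Other parts of the protocol are wider:

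- The subsection on recording, management and reporting: "All adverse events, regardless of severity or expectation, should be meticulously documented in the study records".
- Section VI, item 6: "During CRRT, any adverse events that occur will be observed and recorded, including thrombus formation, bleeding complications, etc".
- Section VI, item 5, with blood pressure taken every 2 hours: "the occurrence of hypotension and other hemodynamic instability events will be recorded".
- Section III, Research Methods, also asks for CRRT-related negative events to be recorded and gives hypotension as its example.
- Section IV, termination criteria, item 1, looks at whether the incidence of serious events related to "treatment such as hypotension, malignant arrhythmias, or death is significantly higher in one group". It also gives example thresholds, including one for infection.
- The subsection on serious adverse events follows each one until it has settled or is stable. Section X says the same of all adverse events.

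Adverse-event incidence is compared between groups by chi-square or Fisher's exact test (Section XI, item 4). It is also an interim indicator (Section IV, item 4) and part of the condition for closing a group (Section IV, item 6).

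**The concern.** A definition of an adverse event should say what is counted. Severity, outcome and relatedness are then recorded about each event. Section VIII puts all three into the definition: the event must be severe, it must reverse, and the reversal is itself evidence of relatedness. The wider recording rules do not clearly override this, because they use the same term that Section VIII has restricted. Staff completing the case report form cannot follow both.

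This matters because safety by flow rate is a stated secondary objective, and Section I names lower blood pressure as the hazard of higher flow in unstable patients. A hypotensive episode managed with CRRT running is the kind of event on which the sections disagree. The count also feeds decisions at the interim analysis as well as the final table.

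The blinding adds to the problem. Section III says that treatment decisions are made by authorised personnel who know the group. If an event counts only when CRRT is stopped urgently, an unblinded decision can determine whether it enters the safety data.

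**Working it through.** The protocol states no figure that depends on this definition, so there is nothing to reproduce. The check is to put the kinds of event beside the rules.

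| Event | Under Section VIII | Elsewhere in the protocol |
|---|---|---|
| Life-threatening event that ends in death without an urgent stop | Not an adverse event: it did not improve | Death is named in the termination rule (Section IV, item 1) |
| Fatal event that forced an urgent stop | Depends on whether the improvement clause covers both limbs or only the life-threatening one | As above |
| Serious infection that persists after CRRT | Fails the improvement condition, with the same ambiguity if it forced a stop | Infection has a termination threshold; serious events are followed until settled or stable |
| Hypotension, not life-threatening, with CRRT running | Meets neither limb | Recorded without condition (Section III; Section VI, item 5); the management text deals with it by measures that do not require stopping CRRT; Section VIII itself lists it as anticipated |
| Minor bleeding with CRRT running | Meets neither limb | Any severity is documented; bleeding is named in the Section XI test |
| Event that begins after the last course of CRRT | Outside the window | No wider window is given: Section VI, item 6, is also limited to CRRT. Survival and renal recovery are recorded later |

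**Does improvement belong to the definition?** The sentence on the window begins by drawing a conclusion. Ending observation with CRRT follows only if adverse events are taken to improve once CRRT stops. That favours reading improvement as a condition of the definition, although the grammar leaves open whether it attaches to one limb or both.

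**Direction of the effect.** Let p be the true incidence in a group and s the share of events that meet the literal definition.

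- Recorded incidence = s × p.
- If s is the same in two groups, the recorded difference is s × (p1 − p2). The ratio p1/p2 does not change. The level and the absolute difference shrink.
- If s differs, the recorded ratio is (s1/s2) × (p1/p2), which can be wrong in either direction. A decision to stop CRRT made with knowledge of the group is one way for s to differ.

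**What this means for the thresholds.** The example thresholds in Section IV, item 1, are absolute: a level and an excess over the other groups. With a common share s, the true values needed to reach them are the stated values divided by s. The protocol does not give s, so a range is assumed.

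| Event type (stated level / excess) | s = 0.75 | s = 0.50 | s = 0.25 |
|---|---|---|---|
| Bleeding (10% / 5%) | 13.3% / 6.7% | 20% / 10% | 40% / 20% |
| Infection (15% / 5%) | 20% / 6.7% | 30% / 10% | 60% / 20% |

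For example, 10/0.75 = 13.3 and 5/0.75 = 6.7. The table shows how the rule would respond to undercounting. It does not estimate how much undercounting there would be.

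**The case against.** The strongest reply is that the protocol collects much of what Section VIII appears to drop. Death is named in the termination rule. Survival status is recorded after discharge (Section VI, item 7) and survival and renal recovery are compared by group (Section XI, item 5). Hypotension is recorded with no condition that CRRT stops. Events are followed until settled or stable. The primary outcome, filter lifespan, does not depend on the definition. Restricting observation to the treatment period is also a legitimate choice.

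All of this stands, and it rules out the stronger reading that a reader might infer: that deaths, lasting harms and hypotension fall outside the safety comparison altogether. The documents do not support that. Nor can it be said that every fatal event is excluded by definition, because the improvement clause may attach only to the life-threatening limb. A numerical claim that a hypotension excess would be diluted below the termination margins would also fail. The protocol gives no hypotension rates and states no margin for hypotension, and the part of the termination rule that names it works by significance.

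The reply does not settle which events are counted. Recording an episode under physiological parameters does not place it in the adverse-event incidence of Section XI. Comparing survival at the end does not put deaths before the interim review, since Section IV, item 4, does not list survival as an indicator. A later analysis document also could not recover minor events that staff did not log because the protocol told them these were not adverse events.

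**Conclusion.** The point holds as an internal contradiction. Section VIII cannot be squared with Section III, Section IV, Section VI, the recording subsection or the serious-adverse-event subsection. As a result, the numerator of the adverse-event incidence is not fixed for the final test, the interim analysis or the rule for closing a group.

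If the literal definition is followed, the incidence understates harm in level and in absolute difference. With an equal share counted in each group the ratio is preserved. With unequal shares, which knowledge of allocation makes possible, it is not. The size cannot be stated, because the protocol gives neither event rates nor the share that would meet the definition. If the wider recording rules are followed, the undercounting of events during CRRT largely disappears, but Section VIII is then wrong as written. Non-fatal events that begin after CRRT, such as a late infection, stay outside the adverse-event count on either reading.

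**What to change.** Replace the Section VIII definition with one that carries no severity, CRRT-stop or improvement condition, and reconcile Sections III, IV and VI and the two reporting subsections to it. Specifically:

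- Keep improvement after stopping CRRT only as a criterion for relatedness, where Section VIII already lists it.
- Record severity, seriousness, interruption of CRRT and outcome as separate fields.
- State that deaths, unresolved events and recorded hypotension count in the Section XI comparison and in the interim safety review.
- State the observation window explicitly and do not derive it from the improvement clause. Its length is for the sponsor to choose.

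These changes concern recording and counting, and they leave clinical management as it is. The cost is a protocol amendment, revised case-report-form wording and more events to log. Blood pressure is already taken every 2 hours and hypotension is already recorded, so the extra data collection for the main flow-related hazard is small.
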